## Methods

### Study Design

The Optimizing Diet for Better Health (OptHealth) study is a randomized clinical trial (RCT) with a total target sample of 110 participants and 100 completers. The sample size was determined by circulating FGF-21 levels (pg/mL), using a 2-tailed ANOVA design and assuming an SD of 70 [18], 80% power, and an α of .05; a difference of 30% (control group mean 149.4 pg/mL) [27] may be detected with a sample size of 25 participants per group (100 in total). The dropout rate was estimated to be 10%; therefore, 110 participants were recruited. Clinical assessments were performed prior to initiating the intervention and after the 4-week intervention period (Figure 1). All study visits were conducted at the Charles Perkins Centre (CPC)–Royal Prince Alfred Hospital (RPAH) clinic. This study protocol was prepared in accordance with the SPIRIT (Standard Protocol Items: Recommendations for Interventional Trials) guidelines for RCTs [28] (Checklist 1).

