### Statistical Analysis

All statistical analyses will be conducted using R software, with significance set at *P*<.05. The analysis will follow the following two approaches: (1) within-subject comparisons using paired sample *t* tests (via the “t.test” function in stats package) to assess overall changes from baseline (habitual diet) to after intervention and (2) between-group analyses of RCT findings across all 4 groups, maintaining treatment assignment integrity and excluding dropouts.

A 1-way ANOVA will be used to examine across the 4 diet groups in follow-up measurements. A linear model (model 1) will be fitted with follow-up values as the outcome and baseline measurements as covariates to assess the effect of the intervention. A second model (model 2) will further adjust for potential confounders, including age, sex, BMI, and physical activity level.

Self-reported appetite and palatability data specific to each diet will be analyzed using the R package *mgcv* with the gam function [44]. Generalized additive mixed models will be applied to assess the effects of dietary interventions on appetite scores. For BCAA levels and metabolites, relative changes (fold changes) will be calculated as the ratio of final to baseline values. A 1-sample *t* test (null hypothesis of fold change=1) will be used to test whether the change from baseline is significant compared to final. To compare differences in fold change across groups, models will be fitted using follow-up measurements as outcomes, adjusting first for baseline values. A second model will further adjust for covariates such as age, BMI, sex, and physical activity levels. Dropouts will be treated by exclusion for analysis.

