## Results

Recruitment commenced in April 2022, with the original recruitment period planned for completion within 2 years. However, recruitment was delayed due to COVID-19–related lockdowns and associated restrictions. Enrollment was completed in November 2025.

In total, 208 individuals were screened, of whom 195 were eligible to attend the screening interview. Following screening, 109 participants were enrolled and randomized to treatment groups. Of these, 100 participants completed the 4-week intervention, and 9 were lost to follow-up.

Participants’ baseline characteristics are summarized in Table 3; no statistically significant differences were observed across the 4 intervention groups.

**Table 3. T3:** Participants’ baseline characteristics by randomly assigned diet treatment group.

Characteristic	Overall (n=100)	Control (n=25)	BCAA^a^ (n=24)	BCAA+tryptophan (n=26)	BCAA+methionine (n=25)
Age (years), mean (SD)	71.1 (4.2)	71.2 (4.5)	70.7 (4.1)	71.8 (4.3)	70.6 (4.1)
BMI (kg/m^2^), mean (SD)	27.3 (4.0)	27.8 (3.3)	27.8 (4.6)	27.5 (4.3)	26.2 (3.7)
Physical Activity Scale for the Elderly (points), mean (SD)	146.3 (67.9)	157.2 (66.2)	157.2 (65.8)	116.8 (68.6)	155.5 (65.9)
Weight (kg), mean (SD)	74.4 (12.3)	75.1 (9.8)	76.8 (11.6)	73.1 (13.9)	72.8 (13.7)
Body fat (%), mean (SD)	38.9 (8.9)	40.3 (8.6)	38.3 (11.4)	39.4 (7.1)	37.4 (8.2)
Fat mass (kg), mean (SD)	29.1 (9.0)	30.2 (7.5)	29.8 (11.3)	29.1 (8.7)	27.3 (8.4)
Grip strength (kg), mean (SD)	26.6 (9.0)	26.1 (9.8)	27.5 (10.0)	26.9 (8.2)	26.0 (8.4)
High education^b^, n (%)	90 (90.0)	22 (88.0)	22 (91.7)	23 (88.5)	23 (92.0)
Ex-smoker, n (%)	41 (41.0)	9 (36.0)	8 (33.3)	11 (42.3)	13 (52.0)
Born in Australia, n (%)	66 (66.0)	17 (68.0)	14 (58.3)	19 (73.1)	16 (64.0)

a BCAA: branched-chain amino acid.

b High education includes any education obtained after high school, whereas low education includes completion of high school or below.

All outcome data collection has been completed. Data cleaning and statistical analyses are scheduled to commence in March 2026, with final analyses expected to be completed by December 2026. Results from this trial are anticipated for publication in 2027.

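### The t test of the untransformed final/baseline ratio against 1 is biased toward an increase and does not hold its 5% level

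*Protocol article*

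**What the plan says.** The Statistical Analysis section of the protocol article sets out a separate procedure for one family of markers, BCAA levels and metabolites: "relative changes (fold changes) will be calculated as the ratio of final to baseline values". The 1-sample t test then has a "null hypothesis of fold change=1) will be used to test whether the change from baseline is significant compared to final". A null value of 1 belongs to the untransformed ratio; on the log scale it would be 0. The section mentions neither a log transform nor a geometric mean. All analyses are run "with significance set at *P*<.05".

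For the comparison between arms the section says: "To compare differences in fold change across groups, models will be fitted using follow-up measurements as outcomes, adjusting first for baseline values". A second model adds age, BMI, sex and physical activity. The scale of the follow-up measurement in these models is not stated.

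The section also plans paired t tests for overall change from baseline. It does not say whether the 1-sample test of the fold change is run within each arm or across all arms.

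**The concern.** A ratio of two noisy positive measurements is not symmetric about 1. A baseline that is low by chance raises the ratio by more than a baseline that is high by chance lowers it, so the average ratio exceeds 1 even when nothing has happened. A t test of that average against 1 therefore tests a value that is wrong under no change. Its errors lean toward an increase, and more data make this worse, because the bias stays fixed while the standard error shrinks.

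At stake is the reading of within-arm changes in BCAAs and metabolites. A rise may be reported that is partly an artefact, and a real fall may be missed.

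There is also a mismatch in the between-arm step. A model of untransformed follow-up values adjusted for baseline yields a difference in concentration units, although the sentence says that it compares fold changes.

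**Working it through.** **Inputs from the article**
- Tested quantity and null value: final/baseline against 1 (Statistical Analysis).
- Significance level: 0.05, taken as two-sided, so 2.5% in each tail.
- Sample size: the Study Design section states that a 30% difference in FGF-21 "may be detected with a sample size of 25 participants per group (100 in total"). The Results section reports that "100 participants completed the 4-week intervention, and 9 were lost to follow-up", and Table 3 shows 25, 24, 26 and 25 by arm.

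**Assumed input**
- Within-person CV of one measurement: not given for these markers. The range shown is 5% to 40%.

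**Step 1. Expected ratio under no change.** Let ln(baseline) and ln(final) have the same person mean and independent within-person variance s², with s² = ln(1 + CV²). Then ln(final/baseline) is normal with mean 0 and variance 2s², so

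E[final/baseline] = exp(2s²/2) = exp(s²) = 1 + CV².

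At CV 20% this is 1 + 0.04 = 1.04. At CV 30% it is 1 + 0.09 = 1.09.

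**Step 2. Error rates.** The figure to reproduce is the nominal 5%, or 2.5% per tail. The two-sided 1-sample t test was simulated with no true change, using 40,000 replicates at n = 25 and 20,000 at n = 100.

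| Assumed CV | Mean ratio | False increase, n = 25 | False decrease, n = 25 | Total, n = 25 | False increase if pooled, n = 100 |
|---|---|---|---|---|---|
| 5% | 1.0025 | 3.3% | 1.8% | 5.1% | 5.2% |
| 10% | 1.010 | 4.3% | 1.4% | 5.7% | 9.3% |
| 20% | 1.040 | 6.8% | 0.8% | 7.6% | 24.5% |
| 30% | 1.090 | 9.7% | 0.6% | 10.3% | 46.1% |
| 40% | 1.160 | 13.5% | 0.3% | 13.8% | 66.6% |

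The results at n = 24 and n = 26 are close to those at n = 25. The raw-ratio test does not reproduce 5%, except nearly so at the lowest CV, and even there the two tails are unequal.

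**Step 3. Same data on the log scale.** A t test of ln(final/baseline) against 0 gives a total error of 4.7% to 5.3% in every cell, with 2.3% to 2.7% in each tail.

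**Step 4. Dependence on the log-normal model.** With additive normal error on the raw scale and CV 10% to 30%, false increases are 4.1% to 6.8% at n = 25 and 10% to 43% at n = 100. The direction is the same and the size somewhat smaller.

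**Step 5. Real falls.** For a true 10% fall at CV 20% and n = 25, the expected raw ratio is 0.9 × 1.04 = 0.936, so part of the fall is hidden. Power is about 26% with the raw ratio and 44% with the log ratio.

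**Step 6. The between-arm model.** Suppose the supplement multiplies the level by k and control leaves it unchanged. On the raw scale the arm difference is (k − 1) × baseline, which depends on the baseline. A single arm coefficient can only average it, in concentration units. On the log scale the difference is ln k for everyone, and exponentiating it gives the ratio of fold changes.

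**The case against.** Several points can fairly be made for the plan, and most of them limit the concern without removing it.

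- **No certainty of a false rise.** A reader might infer that levels will be declared increased when nothing changed. The numbers do not support that: at 25 per arm and CV up to 40%, at least 86% of null tests reject nothing. This stands.
- **Unknown variability.** Samples are fasting at both visits, so a low CV is possible, and at 5% the total error is 5.1%. This stands for the size of the bias. Its direction does not depend on the CV.
- **Pooling.** A reader might take the n = 100 column as the expected result, since the section speaks of overall changes from baseline. That phrase describes the separate paired t tests. Nothing says that the fold-change test pools the arms, so the column is conditional.
- **The randomised comparison.** A reader might infer a false treatment effect. The between-arm models use baseline-adjusted follow-up values, not the ratio, so they do not carry this bias. The control arm is subject to the same kind of bias, which would alert a careful reader. The paired t tests also hold their level (4.5% to 5.3% with additive error).
- **Scale of the between-arm model.** The article does not say that the values are untransformed, and an unseen analysis plan may specify logs. The mismatch is therefore conditional, and baseline-adjusted follow-up is in any case a valid comparison of arms.
- **Importance.** A reader might treat BCAA levels as the formal check of exposure. The article does not give them that role, and they are not among the measures listed under Primary Outcome Measurements.

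What remains is that the article itself states the ratio, the test and the null value. These are not details left to another document, and the combination does not keep the stated level.

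**Conclusion.** The concern holds in a limited form. As written, the 1-sample test of the raw ratio has an expected value of about 1 + CV² under no change, so it leans toward an increase. At about 25 per arm, false increases are roughly 3% to 10% for assumed CVs of 5% to 30%, and about 14% at 40%, against a nominal 2.5%. False decreases drop below 2.5%, and true falls lose power. Pooling all 100 completers would raise false increases to about 5% to 67% over the same CV range, but the article does not say that this test pools.

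The sizes rest on assumed CVs, on independent within-person errors and mainly on log-normal values; the direction was the same with additive normal error. The randomised comparison is not biased by the ratio, though on untransformed values it would not estimate the difference in fold change that it is said to compare. Because the affected tests are within-group and on non-primary markers, this should be fixed but does not threaten the primary conclusions.

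**What to change.** Replace the 1-sample test by a t test of mean ln(final/baseline) = 0, and report the geometric-mean fold change with its 95% CI. State whether this is done within each arm or pooled.

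For the comparison between arms, fit ln(final) on arm and ln(baseline), then add the listed covariates in the second model. The exponentiated arm coefficient is then the ratio of fold changes, which is what the sentence says is being compared.

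The cost is a change of wording and a log transform, with no new data. The Results section schedules final analyses for completion by December 2026, so the rule can be settled before those are final. The one drawback is that values below the quantification limit need the usual handling before logs are taken, and that rule should be written down.

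### Testing the raw final/baseline ratio against 1 biases the within-group test of BCAA levels and metabolites toward rises; the log ratio should be tested against 0

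*Protocol article*

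**What the plan says.** The last paragraph of Statistical Analysis in the protocol article sets out a separate before-after analysis for BCAA levels and metabolites: "relative changes (fold changes) will be calculated as the ratio of final to baseline values". The next sentence names a one-sample t test and gives its null value and purpose: "null hypothesis of fold change=1) will be used to test whether the change from baseline is significant compared to final". The section-wide threshold is given as "with significance set at *P*<.05". Neither a logarithm nor a geometric mean is mentioned.

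Two neighbouring analyses matter for the scope. To compare fold change across the four groups, "models will be fitted using follow-up measurements as outcomes, adjusting first for baseline values", so the randomised comparison does not use the ratio as its outcome. The first paragraph of the section also plans paired t tests as the general within-subject method and excludes no outcome from them.

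On numbers, Study Design states that the target difference "may be detected with a sample size of 25 participants per group (100 in total"), and Results reports: "Of these, 100 participants completed the 4-week intervention, and 9 were lost to follow-up". Table 3 gives 24 to 26 completers per arm.

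**The concern.** A ratio is not symmetric about 1. One participant who doubles (2.0) and one who halves (0.5) average 1.25, although on the multiplicative scale nothing has moved. Ordinary within-person and assay variation therefore pushes the mean ratio above 1 when there is no true change. The null hypothesis as written is then false in the very situation that it is meant to represent.

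The bias points in the direction in which the supplement is expected to move circulating BCAAs, and three of the four arms receive BCAAs. A within-group statement that an analyte rose would be made more often than the nominal rate allows. A statement that an analyte fell would be made less often than the data warrant. The arithmetic mean fold change printed beside the test would also be too high.

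**Working it through.** **Inputs from the article.** The tested quantity is final/baseline, one value per participant. The null value is 1, the test is a one-sample t test, and the significance level is .05 (taken as two-sided, because no sidedness is stated for this test). There are 25 participants per arm and 100 completers in all.

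**Inputs that are assumptions.** The article gives no within-person variability for BCAAs or metabolites. Let s be the within-person SD on the log scale. A range of 0.1 to 0.5 is shown, with lognormal data. The article does not say whether the test is run per arm or over all arms, so n=25 is the main case and n=100 a conditional one.

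**Step 1: direction.** If baseline and final values have the same positive distribution, the mean of log(final/baseline) is 0. By Jensen's inequality, E[final/baseline] ≥ exp(0) = 1, with equality only if every participant is unchanged. This needs no lognormal assumption.

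**Step 2: size of the shift.** With independent within-person noise at each visit, the log ratio has variance 2s². In the lognormal case E[ratio] = exp(2s²/2) = exp(s²):

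- s=0.1: exp(0.01) = 1.01
- s=0.2: exp(0.04) = 1.04
- s=0.3: exp(0.09) = 1.09
- s=0.4: exp(0.16) = 1.17
- s=0.5: exp(0.25) = 1.28

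**Step 3: error rate with no true change.** Log ratios were drawn from N(0, 2s²), with at least 40,000 simulated samples per cell. The raw ratio was tested against 1 and the log ratio against 0. The nominal rate is 2.5% in each direction. Repeat runs differ by at most about half a percentage point.

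| s | n=25: false rise | n=25: false fall | n=25: total | n=100: total (only if arms are pooled) |
|---|---|---|---|---|
| 0.1 | 4.2% | 1.5% | 5.7% | about 10% |
| 0.2 | 6.7% | 0.8% | 7.5% | about 25% |
| 0.3 | 10.1% | 0.5% | 10.6% | about 48% |
| 0.4 | 14.2% | 0.3% | 14.5% | about 70% |
| 0.5 | 18.7% | 0.2% | 18.9% | about 85% |

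At n=25 and s=0.2, rises make up 6.7/7.5 = 89% of the false positives. The log-ratio test stays at about 5% in every cell.

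**Step 4: power at n=25 for a true log change of −0.15**, a fall of 1 − exp(−0.15) = 14%:

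| s | raw ratio vs 1 | log ratio vs 0 |
|---|---|---|
| 0.1 | 99.7% | 99.9% |
| 0.2 | 51% | 72% |
| 0.3 | 16% | 40% |

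For the mirror-image rise, exp(0.15) − 1 = 16%, the raw-ratio test at s=0.3 rejects about 68% of the time against 40% for the log ratio.

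**Step 5: a different data model.** With truncated normal data, between-person CV 0.2 and visit-to-visit correlation 0.5 (again assumptions), the mean ratio under no change is 1.023. False rises and falls are 5.3% and 1.1% at n=25. A paired t test on the differences holds about 5% on such data. The pattern is not a product of lognormality.

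**The case against.** The strongest case on the other side is that the flaw is narrow and often small. Most of that stands.

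- **Small for stable analytes.** In one arm of 25 with s=0.1, total error is 5.7% and almost no power is lost. A reader might infer that a false rise is easy to obtain for any analyte, or that falls go unseen. Neither follows: error passes 10% only at about s=0.3, and the loss of power for falls is material only when variability is high.
- **Pooling.** The rates of 25% and more at n=100 hold only if all completers are tested together. The article does not say that they are. Its reference to overall change belongs to the paired t tests.
- **Another before-after test may cover the same data.** The general paired t tests may also apply to BCAAs and metabolites, and they do not carry this bias. It would go too far to say that the section contains no sound before-after test. But the method that it names specifically for these analytes is the ratio test.
- **Primary and randomised conclusions.** A reader might infer that the main findings are at risk. They are not. The primary outcomes are appetite (self-report, FGF-21, ghrelin) and dietary intake, and the group comparisons use baseline-adjusted follow-up values.
- **A separate analysis plan may specify logs.** A fold change of 1 is also how the null of a log-ratio test reads after back-transformation. This is the weakest point, because the article defines fold change as the plain ratio and mentions no transform.

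**Conclusion.** The point holds for the within-group one-sample test of BCAA levels and metabolites, and for the arithmetic mean fold changes reported with it. The null value of 1 is wrong for the mean of a raw ratio. The bias is toward rises whatever the variability.

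The size rests on an assumed s and, in the main case, on testing one arm of 25 with lognormal data. Total error then runs from about 5.7% (s=0.1) to about 19% (s=0.5), nominal 5%. The mean fold change under no effect runs from 1.01 to 1.28. This is a definite but secondary error that is worth correcting because the correction is almost free.

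**What to change.** Replace the two sentences on fold change with text such as: for each participant compute log(final/baseline); test whether the mean log ratio is 0 with a one-sample t test; report the back-transformed geometric mean fold change with its 95% CI in place of the arithmetic mean ratio. State in the same place whether the test is run within each arm or over all completers.

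The cost is one sentence and one line of R, with no new data. Reported fold changes become slightly smaller, because a geometric mean lies below an arithmetic mean. Outcome data collection is complete and the article schedules the final analyses to finish by December 2026, so the change should be dated and recorded before any fold-change results are examined.

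### Excluding all nine dropouts makes the group comparison completers-only and would throw away any appetite and intake records they left; the likely bias is modest

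*Protocol article*

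**What the plan says.** The Statistical Analysis section gives the rule twice. The between-group analyses are described as "maintaining treatment assignment integrity and excluding dropouts", and the section closes with "Dropouts will be treated by exclusion for analysis". Neither statement makes an exception for participants who left after contributing records.

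The same section plans a linear model of the follow-up value on baseline (model 1), a version with further covariates (model 2), and generalized additive mixed models for the appetite and palatability scores. The Abstract speaks of linear mixed models for the intervention effects.

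The Results section gives the outcome of follow-up: "109 participants were enrolled and randomized to treatment groups", and then "100 participants completed the 4-week intervention, and 9 were lost to follow-up".

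**The concern.** Dropping out happens after randomisation. If the analysis set is defined by staying to the end, those who remain keep their assigned labels, but the arms compared are no longer the full groups that randomisation made alike.

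Three features of this trial make that more than a formality:

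- Participants and coordinators know the allocation, and the Limitations paragraph concedes that this may affect self-reported outcomes.
- Burden differs by arm. Control takes no supplement and the other arms take between three and six units a day (Randomization and Intervention).
- Appetite and food intake are primary outcomes, and poor appetite, dislike of the food or poor tolerance are plausible reasons for leaving a provided-diet study.

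The rule also wastes information. Appetite and intake are recorded throughout the four weeks, so someone who left in week 3 may have usable primary-outcome data from weeks 1 and 2.

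**Working it through.** **1. The counts.** 109 − 9 = 100, and the arms of Table 3 give 25 + 24 + 26 + 25 = 100, so the article's figures agree. Analysed: 100/109 = 91.7%. Excluded: 9/109 = 8.3%. The Study Design section allowed for 10%.

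**2. What the rule discards, by outcome.**

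| Outcome | When recorded | What a dropout may have left |
|---|---|---|
| Appetite scores | Days 4, 11, 18, 25 | A partial series: 0 to 9 × 4 = 36 scores in all |
| Energy intake | Booklet over the four weeks | Recorded days up to leaving |
| FGF-21, ghrelin and other blood measures | Baseline and final visit | Baseline only |

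The article does not say when the nine left, so the amount of on-treatment data lies anywhere between none and these limits.

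**3. Size of a possible bias.** FGF-21 is the only primary measure with a stated SD and target difference, so it serves as the illustration. No such figure can be given for appetite or intake.

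Inputs from Study Design: SD 70 pg/mL; control mean 149.4 pg/mL; target difference 30%, so 0.30 × 149.4 = 44.82 pg/mL; 25 per arm.

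Assumption, not in the article: dropouts would have differed from completers by 0.5 to 1 SD, that is 35 to 70 pg/mL, in the same direction in every arm.

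Shift in an arm's mean = (number lost / number randomised to the arm) × gap.

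- *Three of 27 lost in one arm, none in the other (assumed).* 3/27 × 35 = 3.9 and 3/27 × 70 = 7.8 pg/mL. Divided by 44.82, this is 9% to 17% of the target difference.
- *Most uneven split compatible with the design.* With blocks of 4 within each sex and every envelope used in order, 109 participants put 26 to 28 in each arm. Subtracting the completers in Table 3 gives losses of 1–3 (control), 2–4 (BCAA), 0–2 (BCAA+tryptophan) and 1–3 (BCAA+methionine). For 4 of 28 against none, 4/28 × 35 = 5.0 and 4/28 × 70 = 10.0 pg/mL, or 11% to 22% of the target difference.
- *Equal proportions lost in both arms.* The shifts cancel and the contrast does not move.

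For scale, the standard error of an unadjusted two-arm difference is 70 × √(2/25) = 19.8 pg/mL. The first case is 3.9/19.8 = 0.2 to 7.8/19.8 = 0.4 standard errors. The second is 5.0/19.8 = 0.25 to 10.0/19.8 = 0.5.

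**The case against.** The case for leaving the rule alone is substantial.

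- **The loss is small.** It is 8.3%, below the 10% planned for. No reasons for leaving are given, and losses by arm may be in the flow diagram, which is not shown here. Differential dropout is therefore a possibility, not an observation.
- **Assignment is respected among those who remain.** The phrase about assignment integrity can be read as analysing everyone with follow-up in the arm to which they were randomised. Nothing in the section removes poor compliers or moves anyone between arms.
- **For FGF-21 there is little to recover.** A person lost to follow-up presumably has no final sample. With two time points, a mixed model with a common baseline mean gives nearly the same contrast as the planned baseline-adjusted model under missing at random. Neither corrects for people who left for reasons tied to the unseen outcome.
- **Sensitivity analyses are often left to an analysis plan**, which is not shown.

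All of this stands, and it limits the point. It does not answer the rule itself, which is a positive choice stated twice, without exception, and which covers two primary outcomes with data collected during treatment.

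A reader might infer that the exclusion invalidates the randomised comparison, or that collected FGF-21 results are being thrown away. The documents support neither. A reader might also add that Table 3 covers only completers, or that Study Design says "therefore, 110 participants were recruited" while 109 were randomised. Table 3 prints its denominators openly, and 110 is also given as the target sample. Both are reporting matters that change no result.

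**Conclusion.** The point holds in limited form. As written, the plan yields a completers-only comparison on 100 of 109 randomised participants. It would discard any appetite scores and intake days that the nine recorded before leaving, although the method it names for appetite can use them.

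For measures taken only at baseline and the end, the weakness is different: the result depends on an untested assumption about nine missing final values.

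The likely bias is modest. For FGF-21 the illustration runs from no shift to about 10 pg/mL, at most 0.5 standard errors of a two-arm difference. It rests on an assumed gap of 0.5 to 1 SD in a common direction and on assumed losses by arm; gaps in opposite directions could add up to more. Adjustment for baseline would remove any part of the bias that baseline FGF-21 explains. The wording of the rule is certain. The harm is not, because timing, reasons and arm-level losses are not visible in the text. The change is worth making but not critical.

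**What to change.** Replace the sentence "Dropouts will be treated by exclusion for analysis", and the matching words in the between-group approach, with a rule to this effect:

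> All randomised participants are analysed in the arm to which they were assigned. Appetite scores and intake records are used for every day on which they are available, including those made before a participant left. For measures taken only at baseline and final assessment, the baseline-adjusted model is fitted to participants with a final value, and a delta-adjusted sensitivity analysis varies the assumed difference between missing and observed final values, by arm. A completers-only analysis is reported as supplementary.

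The additive mixed models already planned can carry the appetite series. Intake can be analysed by day or week in a linear mixed model, the type named in the Abstract. A participant with no record after randomisation adds nothing to these models and should be accounted for by arm, with the reason for leaving where known.

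The cost is a little more analysis work and no new data. The main models would rely on missing at random, which should be stated; the delta-adjusted analysis shows how far the baseline/final results depend on it. The rule should be fixed before any results by arm are seen.
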